# Protocol for an effectiveness- implementation hybrid trial to assess the effectiveness and cost-effectiveness of an m-health intervention to decrease the consumption of discretionary foods packed in school lunchboxes: the ‘SWAP IT’ trial

**DOI:** 10.1186/s12889-019-7725-x

**Published:** 2019-11-12

**Keywords:** Childhood obesity, Lunchboxes, Children, Child nutrition, M-health, Schools, Hybrid, Randomised controlled trial, Technology

## Abstract

**Background:**

At a population level, small reductions in energy intake have the potential to contribute to a reduction in the prevalence of childhood obesity. In many school systems, there is the potential to achieve a reduction in energy intake through modest improvements in foods packed in children’s school lunchboxes. This study will assess the effectiveness and cost-effectiveness of a multi-component intervention that uses an existing school-based communication application to reduce the kilojoule content from discretionary foods and drinks consumed by children from school lunchboxes whilst at school.

**Methods:**

A Type I hybrid effectiveness-implementation cluster randomised controlled trial will be conducted in up to 36 primary schools in the Hunter New England, Central Coast and Mid North Coast regions of New South Wales, Australia. Designed using the Behaviour Change Wheel, schools will be randomly allocated to receive either a 5-month (1.5 school terms) multi-component intervention that includes: 1) school lunchbox nutrition guidelines; 2) curriculum lessons; 3) information pushed to parents via an existing school-based communication application and 4) additional parent resources to address common barriers to packing healthy lunchboxes or a control arm (standard school practices). The study will assess both child level dietary outcomes and school-level implementation outcomes. The primary trial outcome, mean energy (kJ) content of discretionary lunchbox foods *packed in children’s lunchboxes*, will be assessed at baseline and immediately post intervention (5 months or 1.5 school terms). Analyses will be performed using intention to treat principles, assessing differences between groups via hierarchical linear regression models.

**Discussion:**

This study will be the first fully powered randomised controlled trial internationally to examine the impact of an m-health intervention to reduce the mean energy from discretionary food and drinks packed in the school lunchbox. The intervention has been designed with scalability in mind and will address an important evidence gap which, if shown to be effective, has the potential to be applied at a population level.

**Trial registration:**

Australian Clinical Trials Registry ACTRN:12618001731280 registered on 17/10/2018. Protocol Version 1.

## Background

Excessive weight gain is a leading contributor to the disease burden in Australia and internationally [1, 2]. As such, addressing overweight and obesity and the promotion of healthy eating habits in children and adults is a public health priority [3]. There is evidence that high intake of energy-dense, nutrient poor foods, referred to as ‘discretionary foods’, is a risk factor for obesity [4, 5]. As consumption patterns of these foods in childhood predicts intake in adulthood, establishing healthy dietary patterns in children may help to reduce the future burden of nutrition related chronic disease [6].

Accordingly, leading health authorities and governments internationally support schools to implement healthy nutrition policies and practices to limit the provision and consumption of discretionary foods among school-aged children [7, 8]. Whilst there have been considerable efforts internationally to improve the availability and purchase of healthy foods provided or sold at school via cafeterias [9] and canteens [10], most of the food consumed (86%) at school by students in many countries is brought from home via a lunchbox [11–13]. However, often the foods packed within lunchboxes are high in energy [14]. School lunchboxes in Australia, for example, contain an average of approximately 3000 kilojoules (kJ) and more than 3 serves (1200 kJ) of discretionary foods [14, 15]. Similarly, lunchboxes in the UK and USA also contain excessive discretionary foods [16, 17] with a study conducted in the UK reporting that the majority of lunchboxes (82%) had discretionary choices such as savoury snacks and confectionary [16]. A study in the USA with 129 Year 5 and 6 students reported children with packed lunches consumed significantly more sugar, saturated fat, sodium and overall energy than those consuming school provided meals [17]. At a population level, small reductions in energy intake, equivalent to approximately 420 kJ across a whole day, have the potential to reduce the prevalence of childhood obesity [18]. Given the excessive energy content and frequent inclusion of discretionary food items in children lunchboxes, modest reductions in the packing of these items in lunchboxes is likely to make an important contribution to achieving such a reduction in energy intake [18, 19].

Whilst evidence and Government policy support improving the nutritional quality of foods packed for children, there is currently little evidence regarding interventions targeting improvement in the nutritional quality of school lunchboxes. A systematic review, conducted by the research team, of interventions targeting the nutritional quality of school and centre-based care lunchboxes identified only ten trials including eight randomised controlled trials and two with quasi-experimental designs, [20] all of which tested approaches to supporting parents to pack healthy foods. All studies included a parental knowledge component via pamphlets, posters, workshops and newsletters, with the majority also including a child knowledge strategy via videos, games and curriculum. Interventions also included physical resources such as lunch packs and containers (*n* = 4) and incentives for children to try fruits and vegetables (*n* = 2) [20]. The interventions reported considerable challenges in accessing and engaging parents through these means. The review found inconsistent impacts between lunchbox interventions in relation to the packing of discretionary foods and beverages [20]. A meta-analysis on four of the included studies highlighted a moderate increase in the provision of vegetables, but no change to fruit. However, there were limitations of included studies in the review as consumption across the entire day was not recorded for the majority of studies which make it difficult to determine any displacement of food serves outside of school hours. As such, previous studies have typically reported little impact of lunchbox interventions on child dietary intake [20].

Evidence is emerging regarding the effectiveness of mobile text messaging [21] and app based interventions [22] as a highly scalable, effective and cost-effective intervention approach for improving a variety of health behaviours. To examine proof of concept and feasibility of such an intervention in improving the packing of healthy lunchboxes, a pilot randomised controlled trial (RCT) was undertaken in 12 primary schools [23]. The ‘SWAP IT’ pilot intervention used an existing school mobile communication app, already adopted by schools to communicate with parents, to provide information via push-notifications and messages to encourage parents to ‘swap’ discretionary foods from their child’s lunchboxes to healthier alternatives consistent with the Australian Dietary Guidelines (‘everyday’ foods). The pilot found 68% of 2100 parents opened the messages via the school mobile communication app, and 84% reported the messages provided were useful [23]. Observational measurement of children’s lunchboxes (*n* = 1462) following the pilot intervention found an increase in the mean energy from everyday foods packed in the lunchbox (83.13 kJ, CI = 2.65, 163.61, *p* = 0.04), and a reduction in both the mean energy from discretionary foods (− 211.61 kJ, CI = -426.16, 2.95, *p* = 0.05) and mean total energy of foods packed in lunchboxes (− 131.61 kJ, CI = -317.26, 54.05, *p* = 0.16) among students attending intervention schools compared with control schools [23]. The results demonstrated that the intervention approach is highly feasible, acceptable and holds significant promise for reducing the mean energy of foods packed in school lunch boxes.

Therefore, the primary aim of this study is to assess, via a Type I hybrid effectiveness-implementation cluster RCT [24], the effectiveness and cost-effectiveness of an intervention that makes use of an existing school mobile communication app (SkoolBag) to decrease the energy (kJ) content from discretionary foods and drinks packed in school lunchboxes. The intervention will also assess a range of implementation outcomes including school and parent level adoption, acceptability, feasibility and appropriateness in order to inform strategies for large scale dissemination.

## Methods

### Design

The cluster RCT will be conducted in 36 primary schools (for children aged 5–12 years). A hybrid Type I effectiveness-implementation design will assess intervention effects on dietary related outcomes and factors to inform future dissemination [24].

The research will be conducted and reported in accordance with the requirements of the Consolidated Standards of Reporting Trials (CONSORT) Statement [25]. Primary schools will be randomised to receive either the multi-component m-health lunchbox intervention, or to a control arm (standard school practices) after baseline data collection.

The primary outcome, mean energy (kJ) content of discretionary lunchbox foods and drinks packed in lunchboxes, will be observationally assessed at baseline and immediately post intervention (5 months or 1.5 school terms).

The secondary outcomes:
**Food packed in the lunchbox:** The 1) mean total energy (kilojoules), 2) mean energy (kilojoules) from healthy foods and 3) mean percentage of lunchbox energy (kilojoules) from discretionary and healthy foods and drinks ***packed in the lunchbox*** will be observationally assessed for consenting students across Kindergarten to Year 6 in both groups at baseline and immediately post intervention (5 months).**Lunchbox food consumed at school:** The mean energy content of 4) discretionary food and drinks, 5) healthy food and drinks, 6) mean total energy (kilojoules) of foods and drinks and 7) mean percentage of lunchbox energy (kilojoules) from discretionary and healthy foods and drinks ***consumed at school*** will be observationally assessed for consenting students across Kindergarten to Year 6, from one randomly selected class from each year, in both groups at baseline and immediately post intervention (5 months).**Food consumed outside of school:** For exploratory purposes and to assess any compensatory behaviours, a sub sample of students’ intake outside of school hours and mean overall daily nutrient intake will also be assessed by parents via a short telephone survey, in addition to self-report [26] for consenting students from Years 5 and 6, at baseline and immediately post intervention at 5 months.**Implementation outcomes:** School and parent acceptability, feasibility, adoption and appropriateness will be assessed immediately post intervention (5 months). School engagement will also be measured and a cost-effectiveness evaluation will be conducted subject to assessment of efficacy.

The trial has been prospectively registered (ACTRN12618001731280).

### Setting

The study will be conducted across three local health districts (LHD) in New South Wales (NSW), Australia (Hunter New England (HNE), Central Coast (CC) and Mid North Coast (MNC)). These districts encompass major city, regional and remote areas and comprise 19% of the NSW population [27].

### Sample and participants

Thirty six primary schools located in three LHDs who are current users of the required school mobile communication app (SkoolBag) will be randomised to receive a 5 month (two school terms), multi-component lunchbox intervention or to a control arm (18 schools per arm). The intervention will be delivered to all students attending intervention schools from Kindergarten to Year 6.

### Recruitment

#### Schools

Primary schools catering for students from Kindergarten to Year 6 will be eligible for inclusion if they meet the following criteria: Government schools; located in one of the participating LHD; greater than 120 student enrolments; current users of the preferred school mobile communication app (SkoolBag); and not participating in other nutrition based research studies. Central and secondary schools catering for students aged 13–18 years and schools primarily catering for children with special needs (such as intellectual disabilities) will be excluded. Eligible schools will be randomly ordered using a random number generator in Excel to randomise the order of schools approached and sent a letter of invitation. One week following the invitation, a member of the research team will contact the principal via telephone and seek consent. A face-to-face meeting will also be offered to all schools to outline the requirements of the study. Recruitment will continue until 36 schools consent to participate (see Fig. 1).

**Fig. 1 Fig1:**
[figure not shown]
Consort flow diagram

#### Parents and children

The child/parent recruitment strategy was developed based on our pilot study and reviews of evidence for facilitating participation in school-based research [23, 28]. Following recruitment of schools, all parents with a child enrolled in Kindergarten to Year 6 in consenting schools will be invited to participate in the study evaluation measures. Students will be provided with an information package containing an outline of the study and a consent form. Active parental consent will be required for child participation and parents will be asked, via the consent form, if they are an active user (i.e. downloaded the app) of the school communication app. One week following distribution of the information package, parents who have not returned a consent form will be telephoned by school-employed staff and asked if their child can participate in evaluation measures. A replacement consent form will be sent to parents who provide verbal consent. The research team have experience in recruiting schools and parents using such methods, obtaining response rates of 70–80% in previous trials [29].

### Randomisation and blinding

Following baseline data collection, schools will be randomly allocated to intervention or control via block randomisation on a 1:1 ratio using a computerised random number function. Randomisation will be stratified by the socioeconomic status of school locality using the Socio-Economic Index for Area (SEIFA 2006), as socioeconomic status is associated with child dietary intake [30, 31]. Randomisation will be undertaken by a statistician not involved in contacting schools in the study intervention or assessment. Data collectors and lunchbox analysis dietitians will be blinded, but school principals will be notified of their group allocation.

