*Lunchbox nutrition guidelines*: Participating schools will be asked to adopt and endorse lunchbox nutrition guidelines, consistent with the WHO and the NSW Department of Education Nutrition in Schools policy [38]. A guideline template will be provided to support schools to communicate to the school community. Principal endorsement of guidelines will be promoted to the school community via the SkoolBag app and school newsletters, utilising the authority of the school Principal, to communicate school expectations and normalise healthy lunchboxes. In the pilot, 85% of schools adopted and endorsed such guidelines. With support from a trained dietitian, the development of lunchbox nutrition guidelines will occur in the first term (5 school weeks) of the intervention.*Weekly support messages*: An existing school mobile communication app (SkoolBag) will be used to communicate healthy lunchbox messages to parents/carers. Through the SkoolBag app, content to support the packing of healthy lunchboxes will be sent to parents/carers at weekly intervals over the second school term (10 weeks) via push notifications (electronic messages). The messages are designed to act as prompts and cues to reinforce packing of ‘everyday’ foods children enjoy, provide tips and suggestions to assist parents to pack ‘everyday’ foods that are quick, convenient and low cost, and connect parents with tools and resources to improve their knowledge and skills to swap out discretionary foods and pack ‘everyday’ foods. The messages and embedded videos provide simple instructions on swapping, demonstrate the time needed to pack healthy lunchboxes and assist parents to plan healthy lunchbox swaps. Distribution of the messages via SkoolBag will be managed by the project team, not requiring school time or resources. In the pilot intervention, all ten messages were delivered to all parent users of the SkoolBag app in all schools resulting in the delivery of 11,500 messages to parents [23].*Resources for parents*: Links embedded in the app messages will connect parents to additional resources housed on the program website. These resources provide parents with information regarding health consequences, simple instructions on making healthy lunchbox swaps, and assist in lunchbox planning to address child preference, cost, convenience and food safety. Additional physical resources including a SWAP IT ideas booklet (lunchbox ideas), clear drink bottle for water and an ice-brick to support food safety concerns will also be provided to parents.*Curriculum resources for schools*: Schools will be provided with a short teacher professional learning session outlining the rationale for the study and providing the skills and resources required to deliver the classroom curriculum lessons. Teachers will be provided complimentary stage appropriate curriculum resources and classroom flipcharts, developed by dietitians in consultation with teachers to align with syllabus outcomes to reinforce program messages. The resources are designed to reinforce healthy food preferences and improve students’ nutrition knowledge.

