
### Control

Schools allocated to the control group will participate in data collection only. They will have access to the app but none of the lunchbox intervention content.

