### Primary outcome

Mean energy (kJ) content of discretionary foods packed from the school lunchboxes will be assessed using a valid and reliable lunchbox observational audit, known as the School Food Checklist (SFC), [39, 40] an approach successfully applied in the pilot and deemed highly feasible in assessing foods packed in the lunchbox resulting in 98% of lunchbox photographs being included in the analysis and will be extended to also assess consumption by taking a second photo at the end of the final school break period. On a randomly selected school day, prior to recess, lunch and in-class vegetable and fruit breaks (pre meal assessment) [41, 42], students will be asked to display their lunchbox on their desk and remove all lids from storage containers. To prevent response bias, parents or students will not be aware of the day of data collection. Trained research assistants will take a photograph of each student’s lunchbox at the beginning of the school day prior to any contents being consumed (“foods packed”) and will also write down any ambiguous items to aid analysis. Students will also be asked if they intend to purchase from the canteen that day.

Students will be asked to place unconsumed or partially consumed items back into their lunchbox, after each meal break (in-class vegetable and fruit breaks, recess and lunch). A second photograph will be taken following the final meal break (post meal assessment). Measures of energy consumption will be calculated by subtracting the energy content of foods and drinks remaining in student’s lunchbox at the post-meal assessment from the energy content of foods and drinks in the lunchbox during pre-meal assessment (“foods consumed”).

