The SFC is a previously validated tool shown to be accurate and reliable in measuring energy from food and drinks for the Australian context. The SFC [39, 40] enables assessment of the kJ content and serving size for each lunchbox item. The checklist includes 20 food and drinks categories including main food items such as bread, fast food and leftovers/mixed dishes and snack items such as noodles, packaged snacks, biscuits and crackers, chocolate and lollies, cheese, eggs, dried fruit and nuts, muesli and fruit bars, cakes and buns, muffins and scones, pastries, desserts, yoghurt, fruit, vegetables, milk, soft drink, water and fruit juice. Foods in each category were included based on the frequency of consumption at school for children aged five to 15 years, according to the National Nutrition Survey 1995 [39] and the average kJ per category identified. The SFC will be used to identify the total lunchbox contents and food items in the lunchbox including the kJ content, number of ‘everyday’ or discretionary lunchbox items and the mean cost of lunchbox items. Everyday items refer to food and drink items that are part of the core food groups as determined by the Australian Dietary Guidelines and Australian Guide to Healthy Eating [4]. Food items classified as discretionary choices are items considered to be energy dense with minimal nutritional value such as cakes, chocolate, lollies, crisps, muesli bars and fast food.

Minor modifications were made to the SFC to separately categorise ‘everyday’ and discretionary food choices and updated to reflect the mean cost of lunchbox items at the time the pilot study was conducted (2017). Categories that required adjustment included: biscuit and crackers, cakes and buns, muffins and scones, desserts and packaged snacks. All foods in these categories were individually divided and categorised as an ‘everyday’ or discretionary food by consensus among dietitians. The serve size and kJ per serve information was obtained from FoodWorks Professional Edition V7 (version 7; Xyris Software, Highgate Hill, QLD, Australia), or if unavailable from FoodWorks, via a snack food database created for pre-packaged items. The snack food database was created by dietitians based on a significant array of pre-packaged snacks available in Australian supermarkets and included detailed nutrition information for each food item.

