Trained dietitians will observe each school lunchbox photo and classify each food and drink item according to its SFC category and the serving size. To further aid this process, decision rules developed will be used to ensure standardisation of assessments. Following the analysis of the pre-meal lunchbox photo, dietitians will analyse the post meal photo.

Students who make canteen purchases on the day of data collection will be excluded from analysis. Primary outcome data will be collected at baseline and immediately post intervention (5 months).

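### Assessors are described as blinded, but a drink bottle and ice-brick given only to intervention families may be visible in the follow-up lunchbox photos, so the blinding cannot be relied on at that visit

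*Protocol article*

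**What the plan says.** All of the following is in the protocol article.

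- **Randomisation and blinding.** Schools are allocated after baseline data collection. The section then says: "Data collectors and lunchbox analysis dietitians will be blinded, but school principals will be notified of their group allocation".
- **Intervention, resources for parents.** Besides a booklet of lunchbox ideas, a "clear drink bottle for water and an ice-brick to support food safety concerns will also be provided to parents".
- **Control.** "Schools allocated to the control group will participate in data collection only". On the app: "They will have access to the app but none of the lunchbox intervention content".
- **Primary outcome, photography.** On the assessment day "students will be asked to display their lunchbox on their desk and remove all lids from storage containers". Research assistants photograph each lunchbox and "will also write down any ambiguous items to aid analysis".
- **Primary outcome, checklist.** The School Food Checklist (SFC) covers drinks as well as foods; its list ends with "yoghurt, fruit, vegetables, milk, soft drink, water and fruit juice".
- **Primary outcome, coding.** "Trained dietitians will observe each school lunchbox photo and classify each food and drink item according to its SFC category and the serving size". Decision rules are to standardise this work. The outcome is measured at baseline and again straight after the intervention.

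**The concern.** The article states a safeguard that its own intervention and measurement procedure can undo. The ice-brick is supplied for food safety, so it is meant to travel with the packed food, and the bottle is meant for the child's water. Both go to one arm only, and the outcome is then read from a picture of the open lunchbox.

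If coders can tell the arm, their calls on what an item is and how large the serving is can drift towards the expected result. Such a drift would be systematic. Neither the number of schools nor the number of students would average it out, and it would enter at follow-up only, the visit at which the arms are compared.

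**Working it through.** **Setting the sections side by side**

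1. Baseline photos precede allocation, so they are unaffected.
2. By follow-up the bottle and ice-brick have gone to intervention families, while control schools take part in data collection only. Any visible item that is recognisably trial-supplied points to the intervention arm.
3. The lunchbox is open, on the desk, with lids off. Drinks, water included, are among the things the checklist covers, so drink containers fall within what is assessed.
4. Dietitians identify each item and judge its serving size from that photo. That leaves room for judgement in the primary outcome.
5. Allocation is by school, with 140 students per school planned. A coder who notices the same bottle or ice-brick in a few photos, and knows which photos come from one school, could infer the arm for all of that school's children.
6. Data collectors see the lunchboxes directly at follow-up and write notes that feed the coding, so they too may learn the allocation.

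**Scale: the design's own precision first**

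Inputs from Sample size and power calculations: SD 900 kJ, ICC 0.05, 36 schools (18 per arm, from Sample and participants), 140 students per school, difference 200 kJ, 80% power. The two-sided alpha of 0.05 is in Analysis.

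- Design effect = 1 + (140 − 1) × 0.05 = 7.95
- Effective n per arm = 18 × 140 / 7.95 = 317.0
- Standard error of the difference = 900 × √(2 / 317.0) = 71.5 kJ
- Power = Φ(200 / 71.5 − 1.96) = Φ(0.838) = 79.9%

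The stated 80% reproduces (a t-based version with 34 degrees of freedom gives 77.6%). The sample size is not in dispute; the calculation is needed only for the standard error.

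**Scale: an assumed coding shift**

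The article gives no figure for coder bias, so the shifts below are assumptions. Let b be the net shift between arms. With no true effect, the two-sided type I error is 1 − Φ(1.96 − b/71.5) + Φ(−1.96 − b/71.5).

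| Assumed net shift b | Share of 200 kJ | Share of the 1089 kJ mean | Type I error |
|---|---|---|---|
| 0 kJ | 0% | 0% | 5.0% |
| 10 kJ | 5% | 0.9% | 5.2% |
| 25 kJ | 12.5% | 2.3% | 6.4% |
| 50 kJ | 25% | 4.6% | 10.8% |
| 100 kJ | 50% | 9.2% | 28.8% |

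The net shift is the share of intervention photos coded with the arm in mind times the shift per such photo. For example, half the photos at 50 kJ each gives 0.5 × 50 = 25 kJ, and three quarters at 100 kJ each gives 75 kJ.

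**The case against.** The strongest reply has four parts.

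- **Visibility is inferred.** The article does not say that the items are branded or distinctive, that families use them, or that they sit in the frame. Control children may own clear bottles and ice-bricks too. This stands. A reader might infer that the items will appear and that the blind fails; the text supports only that they may appear and that the blind cannot be relied on.
- **The coder has limited freedom.** Foods in the mixed SFC categories were divided beforehand into everyday and discretionary by dietitian consensus. Serve sizes and energy per serve come from a nutrition database or a packaged-snack database, and decision rules apply. This also stands. A reader might think the everyday/discretionary call is left to each coder; it largely is not. Item identification and serving size remain. Decision rules make coding more uniform but do not conceal the arm.
- **A condensed article omits operating detail.** Photo labels, coding order and cropping may be set out in a fuller document, and the Data Availability section does give each participant a unique identification number. Their absence is accordingly not the point. The point is that an unqualified blinding statement sits beside an arm-specific object in the measured scene. The identification number is described as a confidentiality measure and does not remove that object.
- **Data collectors do not code.** They photograph and note ambiguous items; they do not classify or size foods. Teachers receive flipcharts, but nothing says these are on display at follow-up. So the data-collector route is the weaker one and calls for more careful wording, not a redesign.

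**Conclusion.** The concern holds as a risk. The article says that data collectors and dietitians are blinded, while its own intervention supplies one arm with objects that may be seen in the follow-up photos, and allocation by school lets a few sightings reveal a whole school. The stated blinding cannot be relied on at follow-up.

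The size of any bias is unknown. Under the assumed net shifts of 25 to 100 kJ it would be 12.5% to 50% of the target difference, with a type I error of about 6.4% to 28.8% at the planning standard error of 71.5 kJ. These figures show how sensitive the trial is to a shift; they are no evidence that one will occur. They rest on the items being recognisable, on coders being able to link photos to a school, and on the judgement left after pre-classification and decision rules. The documents do not support the stronger conclusion that the primary outcome is biased. The change is worth making because it is cheap and protects the main result from an avoidable challenge.

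**What to change.** 1. **Photos.** At both visits and in both arms, move ice-bricks and empty or water-only bottles aside before each photo, or crop or mask them before coding. Water carries no energy, so the primary outcome loses nothing.
2. **Energy-containing drinks.** Keep these in frame for the dietitians to code. Taking every drink out of view and having data collectors record type and volume would pass part of the outcome to the people more likely to know the arm, and would lose the photographic record.
3. **Coding.** Give dietitians the photos under IDs that show neither school nor arm, in random order mixed across schools and arms, and across visits too if coding is done after follow-up. Keep each student's pre- and post-meal photos paired, because consumption is the difference between them.
4. **Text.** Reword the Randomisation and blinding section along these lines: *Dietitians coding the photos are blinded to school and allocation by removing or masking trial-supplied items and by coding de-identified photos in mixed order. Data collectors are not told the allocation but may become aware of it at follow-up.*

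The cost is slightly more handling at each photo and coding that is less convenient than working school by school. Some risk remains where a trial-supplied bottle holds an energy-containing drink and has to stay in frame. The intervention, the sample size and the analysis are unchanged.
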